## Abstract

**Background:**

The global burden of type 2 diabetes mellitus (T2DM) and metabolic syndrome (MetS) continues to rise, with these conditions significantly increasing risks of cardiovascular disease, disability, and mortality. Traditional Chinese Medicine (TCM) syndrome differentiation, a cornerstone of TCM practice, guides diagnosis and treatment by identifying patterns of disharmony. However, large-scale studies investigating TCM syndrome patterns in T2DM comorbid with MetS remain scarce.

**Objective:**

This cross-sectional study aims to characterize TCM syndrome profiles in a population diagnosed with T2DM and MetS and evaluate their diagnostic relevance.

**Methods:**

This cross-sectional study will enroll a cohort of 470 participants diagnosed with T2DM and MetS. All participants will undergo comprehensive assessments, including the Syndrome Differentiation Questionnaire for T2DM and MetS, demographic and anthropometric measurements, biochemical profiling (eg, fasting glucose, glycosylated hemoglobin, and lipid panel), dietary measurement (Food Frequency Questionnaire), physical activity measurement (International Physical Activity Questionnaire Short Form), sleep quality evaluation (Pittsburgh Sleep Quality Index), quality-of-life assessment (Audit of Diabetes-Dependent Quality of Life), stroke risk estimation (Framingham Stroke Risk Score), and retinal imaging. Latent class analysis will be used to identify the TCM syndrome patterns. Factor analysis will be employed to identify core TCM syndrome factors. Hierarchical cluster analysis will be performed to classify TCM syndrome elements, and logistic regression will examine associations between syndrome differentiation, metabolic parameters, lifestyle factors, and disease progression.

**Results:**

This trial was registered on November 17, 2024. Participant recruitment for this study was initiated in November 2024. As of October 2025, more than 450 eligible participants have been enrolled and have completed data collection. Recruitment is scheduled to conclude on December 31, 2025.

**Conclusions:**

As the first large-scale clinical study to systematically characterize TCM syndrome differentiation in T2DM-MetS comorbidity, this research will establish syndrome profiles associated with metabolic parameters, lifestyle factors, and disease progression. The findings are expected to provide a framework for integrating TCM syndrome differentiation into chronic disease management, ultimately contributing to personalized treatment strategies and improved patient outcomes in integrative medicine.

**Trial Registration:**

ClinicalTrials.gov NCT06703684; https://clinicaltrials.gov/study/NCT06703684

**International Registered Report Identifier (IRRID):**

DERR1-10.2196/86217

## Introduction

Diabetes mellitus (DM) presents a critical global health challenge, with its prevalence escalating rapidly. As of 2021, approximately 537 million adults were affected, with projections estimating a rise to 783 million by 2045 without effective preventive measures [1]. Type 2 diabetes mellitus (T2DM) constitutes over 90% of these cases, underscoring its significance in the diabetes epidemic [2]. In Hong Kong, T2DM impacts nearly 10% of the adult population, mirroring global trends [3]. Adults with DM exhibit a 2-4 times higher risk of cardiovascular complications compared to adults with no DM [4]. Alarmingly, 65%-85% of patients with T2DM meet the diagnostic criteria for metabolic syndrome (MetS) [5,6], characterized by abdominal obesity, hypertension, dysglycemia, and dyslipidemia [7,8]. MetS impacts 20%-25% of the global population [9] and serves as an independent predictor of mortality among individuals with diabetes. This coexistence exacerbates metabolic abnormalities and increases cardiovascular risk, underscoring the imperative for early diagnosis and intervention to enhance management and prevent chronic complications [10,11].

Although conventional pharmacotherapy targets individual MetS components (eg, hypoglycemics, statins, and antihypertensives), emerging evidence supports Traditional Chinese Medicine (TCM) as a complementary approach. Clinical trials demonstrate that integrating TCM with Western regimens yields superior improvements in anthropometrics (eg, waist/hip circumference), glycemic control (glucose, glycosylated hemoglobin), insulin resistance index, and triglycerides, with minimal adverse reactions [12]. This aligns with a systematic review of 16 randomized controlled trials, where TCM significantly enhanced weight management and metabolic regulation [13]. Mechanistically, TCM compounds modulate lipid metabolism, vascular endothelial function, and insulin sensitivity via the phosphatidylinositol 3-kinase/protein kinase B signaling pathway, peroxisome proliferator-activated receptor pathway, and AMP-activated protein kinase pathway, offering multitargeted correction of metabolic dysregulation [14]. Together, clinical and pharmacological evidence supports TCM’s role in addressing the complex interplay of T2DM and MetS.

TCM practice relies on accurate diagnosis and treatment procedures known as Bian Zheng Lun Zhi (syndrome differentiation followed by treatment procedures). This vital concept involves a comprehensive analysis of clinical information obtained through 4 main diagnostic methods: observation, listening, questioning, and pulse analysis. The integrated data then guides the selection of TCM therapeutic interventions such as acupuncture and herbal formula prescriptions [15]. For DM, different syndromes exhibit distinct metabolic characteristics and corresponding clinical biomarkers, thereby guiding TCM therapies in alignment with this principle [16]. However, consensus on syndrome differentiation among practitioners is often hindered by a lack of standardized terminology [17], and research on syndrome differentiation for T2DM comorbid with MetS remains limited. This study aims to identify prevalent TCM syndromes in individuals with T2DM and MetS. Additionally, it will examine how these syndromes are associated with health-related behaviors (eg, physical activity, diet, sleep) and quality of life. By identifying specific TCM syndrome patterns that will correlate with particular metabolic abnormalities and varying risks of disease progression, this study may enhance diagnosis and guide personalized treatment strategies.

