### Study Outcomes

The primary outcome will be the TCM syndrome differentiation in patients with T2DM and MetS, as assessed by the Syndrome Differentiation Questionnaire for T2DM and MetS (SDQTM). SDQTM is developed according to the Guideline for the Integrated Diagnosis and Treatment of Metabolic Syndrome [20], Guideline for the Integrated Diagnosis and Treatment of T2DM [21], and Guiding Principles for Clinical Research of New Chinese Medicine [22]. It includes 69 items (Textbox 2) that capture disease nature (eg, wind, dryness, yang deficiency) and location (eg, heart, kidney) [23]. Each item is a closed-ended question featuring a ranked scale with descriptors for symptom severity and frequency. Registered Chinese medicine practitioners will administer SDQTM in a face-to-face consultation integrating the 4 TCM diagnostic methods.

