Physical activity levels will be assessed using International Physical Activity Questionnaire-Short Form by recalling the time and days spent on 4 intensity levels (vigorous, moderate, walking, and sitting) over the previous 7 days [24]. Dietary intake will be assessed using a Food Frequency Questionnaire that is developed for older adults in Hong Kong and requires less than 30 minutes to complete [25]. The Pittsburgh Sleep Quality Index, a 19-item instrument, will be used to evaluate sleep quality over a 1-month interval, with its items generating 7 component scores that are summed into a global score ranging from 0 to 21, where higher scores indicate poorer sleep quality [26]. Audit of Diabetes-Dependent Quality of Life assesses diabetes-specific quality of life through 2 overview items and 19 items covering domains that include leisure, work, physical health, social relationships, and living conditions. A mean weighted impact score will be calculated, with lower scores indicating poorer diabetes-specific quality of life [27]. The FSRS will be used to estimate the individual risk of cardiovascular events, calculated based on age, smoking status, use of antihypertensive medications, blood pressure, diabetes status, high-density lipoprotein, and cholesterol levels [28]. Retinal microvasculature will be noninvasively visualized and quantified by fundus photography and computerized image analysis via a cloud-based artificial intelligence platform (Airdoc, Beijing Airdoc Technology Co, Ltd) to analyze its relation to cardiovascular events [29].

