### Statistical Analysis

Statistical analysis will be performed using SPSS (version 29.0; IBM Corp), Python (version 3.13.9), and R (version 4.5.2; R Foundation for Statistical Computing) software. Missing values will be imputed by multiple imputation using the chained equation method. Quantitative data will be summarized as mean (SD) if normally distributed or as median and interquartile range otherwise. Latent class analysis will be used to identify the TCM syndrome patterns. Factor analysis will be used to reduce the dimensions of TCM syndrome elements and explore their underlying structure. Data suitability will be evaluated using the Kaiser-Meyer-Olkin measure and Bartlett's test of sphericity. Principal component analysis with varimax rotation will be employed to extract the common factors. Based on the factor analysis results, hierarchical cluster analysis will be performed to classify TCM syndrome elements. Cluster boundaries will be determined by identifying large distances between successive fusion levels in the dendrogram. The adjusted Rand index will be used for measuring the agreement between classifications.

For the comparison of quantitative data, one-way analysis of variance will be used if the assumptions of normality and homogeneity of variance are met. Otherwise, the Kruskal-Wallis test will be used. Categorical data will be expressed as numbers and percentages, and comparisons will be conducted using the chi-square test or Fisher exact test, as appropriate. Spearman correlation analysis will be employed to evaluate correlations between continuous variables, and Kendall’s tau-b analysis will be used for ordinal variables. Logistic regression will be performed to examine the relationship between syndrome differentiation and MetS components. A 2-sided value of *P*<.05 will be considered statistically significant.

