### Anticipated Principal Findings

Although TCM syndrome distributions in patients with T2DM and MetS have been previously examined separately [16,33,34], this study specifically focuses on their comorbidity. We anticipate that the TCM syndrome profile of T2DM-MetS comorbidity will demonstrate a distinct distribution pattern compared to either condition alone, exhibiting unique relationships with disease duration and severity. Given that both conditions represent independent cardiovascular risk factors, we further hypothesize that specific TCM syndrome patterns will correlate with particular metabolic abnormalities and varying risks of disease progression. Through the combined application of FSRS and retinal imaging, we will be able to quantitatively characterize cardiovascular risks across different syndrome patterns. Furthermore, we expect these TCM syndromes to be influenced by modifiable health behaviors and associated with differences in the quality of life. Collectively, these findings will provide evidence supporting the clinical value of TCM syndrome differentiation in prognostic stratification and personalized management of T2DM and MetS.

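### Items on sleep and eating help define the syndromes that are then tested against sleep and diet scores, so shared content can inflate those associations by an amount the protocol does not fix

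*Protocol article*

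**What the plan says.** The aim is in the Introduction: "it will examine how these syndromes are associated with health-related behaviors (eg, physical activity, diet, sleep) and quality of life". The Abstract (Methods) and the Discussion (Overview) repeat that syndromes will be related to lifestyle factors.

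Study Outcomes describes the SDQTM: "It includes 69 items (Textbox 2) that capture disease nature". Textbox 2 lists the items. One concerns insomnia and dreaming. Two concern eating: one reduced intake with poor appetite, the other excessive eating with easy hunger.

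Study Outcomes also describes the separate measures. The PSQI "will be used to evaluate sleep quality over a 1-month interval", and "Dietary intake will be assessed using a Food Frequency Questionnaire".

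Under Statistical Analysis, "Latent class analysis will be used to identify the TCM syndrome patterns". Factor analysis and hierarchical clustering of syndrome elements follow. Group comparisons of quantitative data use one-way analysis of variance if its assumptions are met; "Otherwise, the Kruskal-Wallis test will be used". The threshold is common to all tests: "A 2-sided value of *P*<.05 will be considered statistically significant".

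Anticipated Principal Findings adds a direction: "we expect these TCM syndromes to be influenced by modifiable health behaviors and associated with differences in the quality of life". Strengths and Limitations says that a cross-sectional design cannot establish causation. It lists recall bias and confounding, but not shared content between the SDQTM and the sleep and diet measures.

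**The concern.** The tests named have independence, or equal distributions across groups, as their null hypothesis. If the insomnia item agrees with the PSQI and carries weight in a syndrome, that null is false even when nothing else in the syndrome has any link with sleep. A small P value then cannot separate two explanations: the syndrome goes with poor sleep as a distinct behavior, or the same complaint was recorded by two instruments.

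The stated aim is the first of these. The article expects such results to support personalized management, so a contaminated association could be reported as a finding about modifiable behavior. The stake is the interpretation of secondary analyses. The description of which syndromes occur, which is the primary outcome, is not affected.

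**Working it through.** **Sample size used below.** The plan's own figure is N=470. Sample Size Calculation gives a prevalence of 11.2%, precision 3%, 95% confidence and 10% nonresponse. With 3% read as the half-width, n = 1.96² × 0.112 × 0.888 / 0.03² = 424.5, rounded up to 425. Then 425/0.90 gives 473 and 425 × 1.10 gives 468, so 470 reproduces to within rounding. It is a precision calculation for a prevalence and says nothing about the association tests. It serves here only as N.

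**Count of overlapping items (Textbox 2).** Of 69 items, 1 is directly about sleep and 2 are about appetite or amount eaten. No item asks about physical activity, so that comparison is not affected.

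**Check 1: a summed score.** Assume m equally weighted, uncorrelated items, of which only the sleep item correlates (at r) with the PSQI. The correlation produced by overlap alone is ρ = r/√m. The chance of P<.05 is about Φ(atanh(ρ)·√(N−3) − 1.96). Example with r=0.5, m=5, N=470: ρ = 0.5/√5 = 0.224, and the chance is 99.8%. The range r = 0.3 to 0.7 is an assumption.

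| Items in score | ρ from overlap alone | Chance of P<.05, N=470 |
|---|---|---|
| 5 | 0.13 to 0.31 | 83% to about 100% |
| 12 | 0.09 to 0.20 | 47% to 99% |
| 69 | 0.04 to 0.08 | 12% to 45% |

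At N=423 (470 × 0.9) the 5-item range is 79% to 100% and the 69-item range 11% to 41%. This shows the mechanism, but it is not the planned pattern analysis: uncorrelated items would not form classes.

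**Check 2: latent classes, as planned.** The simulation settings are all assumptions: N=470; 4 true classes, with 4 fitted; binary items with base frequency 0.2 to 0.5; insomnia item at 40% in every class; r=0.5 between that item and the sleep score; Kruskal-Wallis on the assigned class; 100 runs per setting. Sleep is unrelated to the true classes, so the rate should be 5%.

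| Other items | Class separation (shift in item frequency) | Sleep item in | Sleep item out |
|---|---|---|---|
| 68 | good (±0.12) | 4% | 3% |
| 68 | weak (±0.05) | 35% | 9% |
| 20 | ±0.10 | 47% | 5% |

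With 100 runs the standard error is √(0.05 × 0.95/100) = 2.2 percentage points at 5% and √(0.35 × 0.65/100) = 4.8 points at 35%. The excess in rows 2 and 3 is therefore well beyond simulation error, while 4% and 3% cannot be told apart.

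**Check 3: price of leaving the item out.** With 68 other items and good separation, the insomnia item was made to differ truly by class. Rejection with the item in versus out was 47% versus 29% (40% ± 10 points) and 97% versus 81% (40% ± 20 points).

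**Causal wording.** Anticipated Principal Findings expects syndromes to be influenced by behaviors. Strengths and Limitations rules out causal conclusions from this design. The two do not agree, whatever the size of the overlap.

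**The case against.** The strongest reply is that the damage may be nil. Only 1 of 69 items is about sleep. Latent class analysis weights items by how well they separate classes, and an insomnia item unrelated to the rest would carry little weight. The first row of Check 2 bears this out. A reader might infer that a significant sleep association is largely built in; the documents do not support that. Check 1 gives its highest figures for short, equally weighted sums that the plan does not describe. What stands against the reply is that class separation is unknown in advance, and the factors and elements may rest on few items.

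Statistical Analysis does not name the PSQI or FFQ beside any test, does not say which items enter the models, and reserves its one named regression for MetS components. Item-level handling may sit in a fuller document. That is fair, but the article itself fixes the item list, the derivation and the aim, and it sets no item aside.

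Diet should not be put on a par with sleep. The SDQTM records appetite and hunger as symptoms, whereas the FFQ measures intake, and no figure here quantifies that overlap. A reader might also count the nocturia item as overlapping with the PSQI; the article does not describe PSQI content in enough detail to support this.

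Finally, the SDQTM follows published guidelines, so removing items changes the construct, and Check 3 shows fewer rejections when the association is real. This is a good reason not to make the reduced version the main analysis. It does not argue against reporting it.

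**Conclusion.** The point holds in a limited form. Shared content can inflate the syndrome-sleep association and, to a lesser extent, the syndrome-diet association. The plan neither acknowledges this nor guards against it. The amount cannot be fixed from the documents. Under the assumed settings, false-positive rates for sleep ran from about nominal (4%) to 35% and 47%, and leaving the sleep item out brought them to 3%, 9% and 5%. These rates depend on the assumed number of classes, their separation, binary scoring and r=0.5. The real items are on a ranked scale, and none of these quantities is given in the article.

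The direction in "we expect these TCM syndromes to be influenced by modifiable health behaviors and associated with differences in the quality of life" goes further than the design allows. A reader might infer that the study intends a causal claim. The limitations section and the call for longitudinal research show otherwise, so this is a wording conflict to correct.

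**What to change.** 1. Keep the full-item SDQTM syndromes as the main definition.
2. Prespecify an additional analysis that re-derives or rescores the patterns without the insomnia item for the PSQI, and without the two appetite and hunger items for the FFQ.
3. Report both versions side by side. Describe sleep or diet as associated with a syndrome as a separate behavior only if the association persists without the shared items.
4. In Anticipated Principal Findings, replace the wording of influence with wording of association, and add the shared content to Strengths and Limitations.

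The cost is one extra run of the same code and a few sentences. No new data are needed, and recruitment is unaffected. The reduced version has a slightly different syndrome definition and, as Check 3 suggests, some loss of power, so a null result there should be read with its confidence interval and not as proof of no link.

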## Methods

### Study Design

We present a protocol for a cross-sectional study. This study will be conducted at the Chinese Medicine Clinics of Hong Kong Baptist University in Hong Kong Special Administrative Region, China. Data collection will be conducted over a 12-14 month period, commencing in November 2024.

### Ethical Considerations

This study has been approved by the Research Ethics Committee of Hong Kong Baptist University (REC/23-24/0564) and has been registered at ClinicalTrials.gov (NCT06703684). Volunteers will be required to provide written informed consent. The reporting of this study follows the recommendations of the STROBE (Strengthening the Reporting of Observational Studies in Epidemiology) guidelines [18].

### Study Procedure and Population

We aim to recruit a cohort of 470 adult participants (age ≥18 years) diagnosed with both T2DM and MetS [19]. The inclusion and exclusion criteria are detailed in Textbox 1. Following screening, enrolled participants will proceed to complete the study assessments. Participants who complete all study procedures will receive a transportation allowance of HK$100.

Inclusion and exclusion criteria for participation.
**Inclusion criteria**
Age between 18 and 75 yearsDiagnosed with type 2 diabetes mellitusDiagnosed with metabolic syndrome according to guidelines for the prevention and treatment of type 2 diabetes mellitus in China (2020 edition) from Chinese Diabetes Society. People who meet 3 of the following diagnostic criteria or more can be diagnosed with metabolic syndrome [19]: (1) abdominal obesity, that is, having waist circumference ≥90 cm for males and ≥85 cm for females; (2) hyperglycemia, that is, having fasting blood glucose ≥6.1 mmol/L or 2-hour postprandial glucose ≥7.8 mmol/L, and/or those who have been diagnosed with hyperglycemia and in treatment; (3) hypertension, that is, those with blood pressure ≥130/85 mm Hg, and/or those who have been diagnosed with hypertension and in treatment; (4) fasting triglyceride ≥1.70 mmol/L; and (5) fasting high-density lipoprotein cholesterol <1.04 mmol/LClearly understand the trial and voluntarily sign the informed consent form
**Exclusion criteria**
Diagnosed with type 1 diabetes, steroid-induced diabetes, gestational diabetes, or specific types of diabetesDiabetes accompanied by severe complications such as diabetic nephropathy and diabetic ketoacidosisSecondary obesity (eg, secondary to pituitary inflammation, tumor)Secondary hypertension (eg, pheochromocytoma, renal hypertension)Secondary hyperlipidemia (eg, hypothyroidism, nephrotic syndrome)With severe heart, liver, or kidney disease or bleeding disorders, or with other serious diseases (eg, cancer, dementia)With severe mental disorders, speech, or hearing impairmentsPregnant or lactating femalesCurrently in another clinical trial

### Study Outcomes

The primary outcome will be the TCM syndrome differentiation in patients with T2DM and MetS, as assessed by the Syndrome Differentiation Questionnaire for T2DM and MetS (SDQTM). SDQTM is developed according to the Guideline for the Integrated Diagnosis and Treatment of Metabolic Syndrome [20], Guideline for the Integrated Diagnosis and Treatment of T2DM [21], and Guiding Principles for Clinical Research of New Chinese Medicine [22]. It includes 69 items (Textbox 2) that capture disease nature (eg, wind, dryness, yang deficiency) and location (eg, heart, kidney) [23]. Each item is a closed-ended question featuring a ranked scale with descriptors for symptom severity and frequency. Registered Chinese medicine practitioners will administer SDQTM in a face-to-face consultation integrating the 4 TCM diagnostic methods.

Items of The Syndrome Differentiation Questionnaire for Type 2 Diabetes Mellitus and Metabolic Syndrome (SDQTM).Fatigue and weaknessShort of breath and want of speechSpontaneous sweatingPale or sallow yellow complexionPale lips and fingernailsDizzinessDry throat and mouthSensation of heat in the palms, soles, and chestHot flashes or night sweatsAversion to cold and cold limbsPuffy face and edema of the feetWeak coughSusceptibility to common coldsReduced food intake and poor appetiteAbdominal distension after eatingLower back and knee weaknessTinnitus and deafnessLoose teeth and hair lossDecreased libidoPalpitationsInsomnia and profuse dreamingForgetfulnessBlurred visionLusterless nailsNumbness in the hands and feetDry eyesIrritability or depression with frequent sighingCold pain in the abdomenThirst with desire for cold drinksExcessive eating and easy hungerFullness in chest and hypochondriumDistending pain in the abdomenGeneralized edemaHeavy sensation in the limbsDry mouth and bitter tasteDusky or dull dark complexionPurplish dark lipsSquamous and dry skinFixed painPetechiae on the skinNauseaVomitingItching skinSticky, greasy sensation in the mouthDark yellow or reddish urineFrequent urination in large volumeFrequent nocturiaScanty urineDry hard stoolsLoose stoolsAtonic constipationDark urine and constipationEnlarged tongue with teeth marksPale tongueRed tongue with scant coatingPale, enlarged tongue with a moist coatingRed tongue with yellow coatingYellow and greasy tongue coatingPurplish dark tongue, sublingual vein engorgementSlippery and greasy tongue coatingWeak and forceless pulseThready and weak pulseThready and rapid pulseDeep and slow pulseRapid pulseWiry pulseWiry and slippery pulseChoppy or intermittent pulseSlippery pulse

The secondary outcomes include demographic and anthropometric measurements, blood pressure, fasting glucose, glycosylated hemoglobin, lipid panel (total cholesterol, triglycerides, high-density lipoprotein, low-density lipoprotein), International Physical Activity Questionnaire-Short Form, Food Frequency Questionnaire, Pittsburgh Sleep Quality Index, Audit of Diabetes-Dependent Quality of Life, Framingham Stroke Risk Score (FSRS), retinal imaging, and concurrent medications.

Physical activity levels will be assessed using International Physical Activity Questionnaire-Short Form by recalling the time and days spent on 4 intensity levels (vigorous, moderate, walking, and sitting) over the previous 7 days [24]. Dietary intake will be assessed using a Food Frequency Questionnaire that is developed for older adults in Hong Kong and requires less than 30 minutes to complete [25]. The Pittsburgh Sleep Quality Index, a 19-item instrument, will be used to evaluate sleep quality over a 1-month interval, with its items generating 7 component scores that are summed into a global score ranging from 0 to 21, where higher scores indicate poorer sleep quality [26]. Audit of Diabetes-Dependent Quality of Life assesses diabetes-specific quality of life through 2 overview items and 19 items covering domains that include leisure, work, physical health, social relationships, and living conditions. A mean weighted impact score will be calculated, with lower scores indicating poorer diabetes-specific quality of life [27]. The FSRS will be used to estimate the individual risk of cardiovascular events, calculated based on age, smoking status, use of antihypertensive medications, blood pressure, diabetes status, high-density lipoprotein, and cholesterol levels [28]. Retinal microvasculature will be noninvasively visualized and quantified by fundus photography and computerized image analysis via a cloud-based artificial intelligence platform (Airdoc, Beijing Airdoc Technology Co, Ltd) to analyze its relation to cardiovascular events [29].

